## Data collection methods and procedure

Both qualitative and quantitative methods of data collection will be considered in this study. In phase 1, qualitative study will be conducted for development and design of intervention. In phase 2, baseline data of all the subjects will be collected at the enrollment procedure. The measures including demographic information (age, marital status, current occupation, educational level, income and previous residence), knowledge about and perception of breast cancer and screening, past behavior related to breast cancer screening and distal factors. At the end of the intervention (after three months), the same data will be collected. To see the effect of the intervention, the same data will be collected at the end of the six months.

**3.7.1 Data collection instruments:**

For qualitative part of the study (phase 1 for designing intervention), focus group discussion and in-depth interview guide comprising: women, health providers and health extension workers experience regarding breast cancer, and barriers to and facilitating factors for breast cancer screening. Perception of women’s rational decision/based on critical thinking in breast screening uptake or not

In phase 2, a pretested, structured and translated questionnaire adapted from various breast cancer screening related studies [49, 61, 70-75], based on modified constructs of health belief model will be used as instrument for quantitative study. The translation will be made from English language to Amharic and back translated to English version by different individuals who are blind to the original version of the questionnaires (English version) in order to facilitate reliable responses to underlying questions and keep the original meaning of the instrument. The instrument comprised socio-demographics characteristics, knowledge about breast cancer and screening items with response format of ‘yes’, ‘no’ and ‘don’t know’ assuming score of ‘Yes’=1, ‘No’ or either of ‘don’t know’=0 for every correct item and will be reversed for incorrect items, Cues to breast screening with dichotomized ‘yes’, ‘no’ items and past behavior related to breast cancer and experience of screening items with a mix of nominal and scale measurements. Womens’ health value and Health motivation, perception of susceptibility to and severity of breast cancer, perceived benefit breast screening, perceived barrier of screening and self-efficacy to take screening and related health care items all of which eliciting responses on a five-point Likert scale format, ranging from `strongly disagree' to `strongly agree' will be incorporated. Each of the responses will be scored as: `strongly disagree' = 1, `disagree' = 2, `undecided/not sure' = 3, `agree' = 4 and `strongly agree' = 5. After reversing for negatively worded items, scores will be summed for each respective concept.

Factor analysis will be done for validation of the instrument. For this, Eigen value of greater than one will be considered for construct validity and confirming constructs of the model. Factor loading score of ≥ 40% and rotation with varimax method will be considered to identify to which construct each item belongs that items with factor loading score of less than 40% will be rejected. After constructs are decided on those constructs previously lacking names will be named according to the concept the loaded items inferred of the constructs. To ensure reliability of the scales, internal consistency of items will be seen separately for each construct identified using cronbanch’s alpha score of ≥ 70% as cut of point. Items correlation with total correlation of score ≥ 30% will be acceptable cutoff point and less will be avoided.

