**Control group (n=405)**

- Usual care (services)
- Welcome message
- No continuous follow up

Phase 2 follow up assessment at the end of 3^rd^ and 6^th^ month

**Main outcome:** Screening Uptake **Secondary outcomes:** Increased knowledge, attitude and intention to screening

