**3.6.3. Outcome measures:**

Outcomes will be compared between intervention and control arms, and between different time points of each arm. The primary outcomes include breast cancer screening behavior/intention (mammography use, breast self-examination and breast clinical exam), secondary outcomes include increased awareness for breast cancer and its screening and developing health motivation. Another outcome is, not a must, community based intervention mechanism using HBM constructs effectiveness. The outcome for qualitative part will be measured with respect to constructs of health belief model and anomalies treated accordingly. If anomalies are there, they will be used in questionnaire amendments to be included in quantitative and treated as distal factors in the conceptual framework.

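### Read literally, the reversed coding of the knowledge items gives *don't know* a point on every false statement, which inflates the score and attenuates the measured effect of the education

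*Protocol*

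**What the plan says.** Section 3.7.1 (Data collection instruments) describes the "knowledge about breast cancer and screening items with response format of ‘yes’, ‘no’ and ‘don’t know" options. On statements that are correct, *yes* earns 1. The rest of the rule reads: "No’ or either of ‘don’t know’=0 for every correct item and will be reversed for incorrect items". No other part of the Protocol says separately how *don't know* is scored on an incorrect statement.

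The score is used in three ways:

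- **Outcome.** The participant flow chart (Fig. 3) lists as secondary outcomes "Increased knowledge, attitude and intention to screening". Section 3.6.3 words it slightly differently: "secondary outcomes include increased awareness for breast cancer and its screening and developing health motivation".
- **Repeated measure.** Section 3.7 has knowledge measured at baseline and again later: "At the end of the intervention (after three months), the same data will be collected". The same is planned at six months.
- **Predictor.** Section 3.6 places general knowledge among the predictor variables, and the conceptual framework (Fig. 1) shows it as a modifying factor.

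**The concern.** A knowledge score should separate women who know from women who do not. The three-option format allows this, because *don't know* is an open admission of not knowing. On true statements the rule respects that and gives *don't know* nothing. On false statements a literal reversal turns the shared 0 into a shared 1, so the same admission earns full credit.

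The intervention is educational, and moving women from *don't know* to a right answer is one of the changes that the score has to detect. If the point has already been given at baseline, that change cannot add to the score on false items. Baseline and control-arm scores are raised, and the arm difference shrinks whenever the education lowers the share of *don't know* answers more than usual services do. The same mismeasured score would enter the regression for predictors of screening behaviour in section 3.9.

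**Working it through.** The Protocol states no figure that depends on this rule, so there is none to reproduce. The check follows the rule through its consequences.

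**Inputs.** The response options and the code for true items come from section 3.7.1. The share of false items (*f*) and the response mixes are not given in the text at hand and are assumed below.

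**Step 1: the two codings of a false statement.**
- Literal reversal: *yes* 0, *no* 1, *don't know* 1.
- Right answer only: *yes* 0, *no* 1, *don't know* 0.

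**Step 2: change in score for each move on a false statement.**

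| Move | Literal reversal | Right answer only |
|---|---|---|
| *Don't know* to *no* | 0 | +1 |
| *Yes* to *no* | +1 | +1 |
| *Yes* to *don't know* | +1 | 0 |
| *Don't know* to *yes* | −1 | 0 |
| *No* to *don't know* | 0 | −1 |
| *No* to *yes* | −1 | −1 |

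**Step 3: the mean on one false item.** Under literal reversal the mean is P(*no*) + P(*don't know*) = 1 − P(*yes*). Under right-answer-only scoring it is P(*no*). The literal gain is therefore the fall in *yes*, and the proper gain is the rise in *no*. Since the three shares sum to 1, the gain that goes missing equals the fall in *don't know*.

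| Assumed mix, *yes*/*no*/*don't know* (%) | Literal gain | Right-answer-only gain | Missing gain = fall in *don't know* |
|---|---|---|---|
| 50/20/30 to 10/80/10 | 0.50 − 0.10 = 0.40 | 0.80 − 0.20 = 0.60 | 0.20 |
| 30/20/50 to 10/80/10 | 0.30 − 0.10 = 0.20 | 0.80 − 0.20 = 0.60 | 0.40 |
| 10/20/70 to 10/80/10 | 0.10 − 0.10 = 0.00 | 0.80 − 0.20 = 0.60 | 0.60 |

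The literal gain is zero when the share answering *yes* does not change, as in the last row.

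**Step 4: the whole score, extreme case.** Take the score as a fraction of its maximum. A woman answering *don't know* throughout scores (1 − *f*) × 0 + *f* × 1 = *f* under literal reversal, and 0 under right-answer-only scoring. All right scores 1 under both. Her measured gain is 1 − *f* instead of 1, so the loss is *f*: 0% at *f* = 0, 10% at 0.10, 25% at 0.25 and 50% at 0.50.

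**The case against.** The strongest reply is that the sentence may mean only that the keyed answer switches from *yes* to *no*, with *don't know* still uncredited. Grouping *don't know* with the uncredited answer on true items fits that intent. The reading is possible, but the text does not state it, and anyone who codes the data from this sentence as written would credit *don't know*. It follows that a reader should not infer that the investigators meant to reward not knowing. The Protocol shows a badly fixed rule, not that intention.

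A reader might also infer that learning on false items cannot show at all. That goes too far: correcting a misconception, *yes* to *no*, gains a full point under either coding. Nor can the 10% to 50% losses be taken as the expected loss. They describe only a woman who goes from all *don't know* to all right, and neither the share of false items nor the response mix is known. If few items are false, the effect is small.

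It can be said too that section 3.7.1 drops items with loadings below 40% or item-total correlations below 30%, which might catch the affected items. The section does not say expressly that these checks cover the knowledge items. If they do, they would at best remove sound false statements and would not correct their scoring.

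Finally, scoring detail is often left to an analysis plan. Here the Protocol itself states the rule, so the point concerns what is stated and not what is absent.

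**Conclusion.** The point stands on the literal wording. *Don't know* earns the same credit as rejecting a false statement. On those items a move from *don't know* to *no* adds nothing, a move from *yes* to *don't know* gains a point, and only *yes* to *no* shows as learning. The score is inflated for women who do not know, and the measured education effect is attenuated to the extent that women start at *don't know* and leave it.

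Per false item, the missing gain equals the fall in the share answering *don't know*: 0.20 to 0.60 in the three assumed mixes. Over the whole score, the loss in the extreme case equals the share of false items. Both results rest on assumed inputs and on the literal reading.

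This touches a secondary outcome and a predictor. The primary outcome, screening uptake, and the sample size do not depend on it. The change should be made, but the point does not threaten the trial's main comparison.

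**What to change.** Replace the scoring sentence in section 3.7.1 with: *score 1 only for the right answer (yes on true statements, no on false statements); score 0 for a wrong answer or don't know on every item.*

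This is right under either reading of the present text. It costs one sentence and one line of scoring code. The questionnaire and data collection do not change, and responses already recorded in the three options can be rescored.

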### Research Questions and Hypothesis

- - 1. **Research Questions**
       1. What is the distribution of breast screening behavior in different predictor variables (socio-demographic, socio-economic, and perceptions)?
       2. Are the individual Health Belief Model constructs, confidence, health motivation, perceived susceptibility, perceived severity, perceived benefits, and perceived barriers, significant predictors of breast screening behavior?
       3. Does the community based health education intervention bring difference between intervention and controlled groups on breast screening behavior?
       4. Why women are not using breast cancer screening services or exploring barriers and facilitating factors for breast cancer screening behavior among reproductive age women?
    2. **Study Hypothesis**

1. There is a difference in breast screening behavior in different predictor variables (socio-demographic, socio-economic, perceptions) about breast cancer screening behavior among reproductive age women
2. There is a difference in breast screening behavior between intervention and control groups

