**The major constructs of the HBM and their definitions:** (a) Perceived Susceptibility: One's belief of the chances of getting a condition a health condition (breast cancer) (b) Perceived Severity: One's belief of how serious a condition and its consequences are or of leaving it untreated including evaluations of health and social threats. The combined effect of both perceived susceptibility to and severity of a health condition (breast cancer) result in perceived threat from ill health (severity of breast cancer) (c) Perceived Benefits: the subjective perception of the ease of the effectiveness of strategies designed to reduce the threat of illness. (d) Perceived Barriers: One's belief in the tangible and psychological costs of the advised behavior or subjective perception of perceived or real barrier of someone feels to take a recommended health action (breast screening). (e) Cues to Action: strategies to activate "readiness" to take a recommended health action (either physiological (e.g. swelling) or environmental (e.g., media peers) (f) Self-Efficacy: Confidence in one's ability to take action or one’s belief in being able to perform the recommended action [26].

In addition to the above basic constructs originators and researchers put some variables as modifying factors as they can influence individual perceptions and thus, indirectly health-related behaviors. These variables are of demographic, socio-psychological, health motivation and structural [25].

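### Section 3.7.1 scores pre-set Health Belief Model concepts but lets an eigenvalue-above-one factor analysis redraw them, which can split or shorten scales when items load moderately

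*Protocol*

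**What the plan says.** Section 3.7.1 lists the concepts measured on five-point Likert items: health value and motivation, susceptibility, severity, benefit, barrier and self-efficacy. After reversing negatively worded items, it adds the scores within each concept. The concepts are therefore known before data are collected. Research question 2 depends on them: "Are the individual Health Belief Model constructs, confidence, health motivation, perceived susceptibility, perceived severity, perceived benefits, and perceived barriers, significant predictors" of screening behaviour? Section 3.6.3 also names health motivation as a secondary outcome.

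The validation paragraph of 3.7.1 then sets a different procedure:
- Number of factors: "Eigen value of greater than one will be considered for construct validity and confirming constructs of the model".
- Assignment of items: "Factor loading score of ≥ 40% and rotation with varimax method will be considered to identify to which construct each item belongs".
- Deletion: "items with factor loading score of less than 40% will be rejected".
- New factors: "those constructs previously lacking names will be named according to the concept the loaded items inferred of the constructs".
- Reliability: each construct identified is checked against a Cronbach "alpha score of ≥ 70% as cut of point", with an item-total correlation of at least 0.30.

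**The concern.** A procedure that chooses the number of factors from the data, moves items between them and deletes items cannot confirm a structure stated beforehand; it puts another in its place. The protocol thus holds two scoring keys, one fixed by the model and one derived from the data, without saying which governs. This conflict exists whatever the quality of the items.

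The retention rule adds a practical risk. Eigenvalue above one is a population criterion applied to a sample correlation matrix, and sampling noise can lift surplus eigenvalues over the limit. If one concept is spread over two factors, its items are scored apart, and each part is shorter and less reliable. Research question 2 would then be answered on scales that are no longer the named constructs, or some constructs would be missing. Health motivation could be measured on a shortened scale.

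**Working it through.** The protocol gives no figure to reproduce. The check asks when the eigenvalue rule misjudges the number of constructs at this sample size, and what the protocol's own reliability filter then does.

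**Inputs from the protocol.** Up to 810 respondents; five-point items; eigenvalue above 1; varimax; loading cut 0.40; alpha at least 0.70; six constructs in research question 2.

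**Assumptions.** 4 to 10 items per construct; a typical loading λ of 0.4 to 0.7 (single items within 0.1 of it); correlation between constructs 0.3 unless stated. The questionnaire is not shown, so these are ranges and not estimates.

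**Step 1: hand check.** With equal loadings, the surplus population eigenvalues equal 1 − λ², which is below one. In a sample of n with p items, the largest of them rises to about (1 − λ²)(1 + √(p/n))², the Marchenko–Pastur upper edge. For 6 constructs with 8 items, p = 48 and √(48/810) = 0.243, so the multiplier is 1.243² = 1.546.
- λ = 0.5: 0.75 × 1.546 = 1.16, above one, so surplus factors are expected.
- λ = 0.6: 0.64 × 1.546 = 0.99, borderline.
- λ = 0.7: 0.51 × 1.546 = 0.79, so none is expected.

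**Step 2: simulation.** 60 data sets per setting, n = 810, 6 or 7 true constructs, five-point items. The first value is the hand check for 6 constructs; the second is the share of data sets with too many factors.

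| λ | 4 items | 6 items | 8 items | 10 items |
|---|---|---|---|---|
| 0.4 | 1.15; 98–100% | 1.23; 98–100% | 1.30; 98–100% | 1.36; not run |
| 0.5 | 1.03; 18–62% | 1.10; 100% | 1.16; 100% | 1.21; 100% |
| 0.6 | 0.88; 0% | 0.94; 0–17% | 0.99; 55–90% | 1.04; 100% |
| 0.7 | 0.70; 0% | 0.75; 0% | 0.79; 0% | 0.82; 0% |

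The two agree. At λ = 0.65 there was no excess with up to 8 items, and an excess in 12% (6 constructs) or 58% (7 constructs) of data sets with 10. Parallel analysis gave the true number in 95–100% of data sets in every setting tested (λ from 0.5 to 0.7).

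**Step 3: effect on the scales.** With 6 constructs and loadings spread over 0.4–0.7, the rule kept about 8 factors with 7 items each, leaving 4.0 of 6 constructs intact. With 9 items each it kept about 10 factors, leaving 2.8 of 6 intact.

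**Step 4: the alpha filter.** For k items of equal loading, alpha = kλ²/(1 + (k − 1)λ²). Take k = 10, λ = 0.5:
- Whole scale: 2.5/3.25 = 0.77, which passes.
- Split into halves of 5: 1.25/2.00 = 0.63, which fails.

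In simulation at this setting (6 constructs, simulated alpha of the intended scales 0.74), about 14.5 factors were kept and on average 4.35 passed alpha. With 8 items at λ = 0.5 about 11 were kept and 2.3 passed; there the intended scales average alpha 0.70, right on the limit, so some of that loss would occur anyway. At λ = 0.6 with 8 or 10 items, as many factors passed as there were true constructs. The mean number passing never exceeded the true number.

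**Step 5: rotation.** Raising the construct correlation from 0 to 0.5 did not increase over-extraction and had little effect on splitting. When the right number of factors was kept, the summed scores still correlated at 0.16–0.27 for a true correlation of 0.3.

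**The case against.** Five points can fairly be made for the plan.

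1. *The reliability filter.* Alpha and item-total limits stand in the same paragraph. A reader might infer that spurious constructs would be named and enter the analysis; the filter largely stops that, as step 4 shows. It does not protect a sound scale that has been split, because the fragments are what fail.

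2. *Varimax.* A reader might infer that orthogonal rotation forces related constructs apart. It does so only for the factor axes. Scores are item sums and stay correlated. The statement in Chapter Two that "The combined effect of both perceived susceptibility to and severity of a health condition (breast cancer) result in perceived threat" describes two inputs acting together, which does not require them to be correlated. Rotation is a secondary matter.

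3. *Item quality.* The 0.40 limit is a rejection floor and not the expected loading. The instrument is pretested and adapted from earlier studies. At λ = 0.4, alpha is 0.96/1.80 = 0.53 with 6 items and 1.28/2.12 = 0.60 with 8, so such scales would fail under any retention rule. This stands. The exposed range is longer scales with moderate loadings, which a translated instrument compiled from several sources could have.

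4. *Purpose.* The model is deliberately modified, and Phase 1 may add items without a construct (3.6.3). Exploring and naming those is reasonable. It does not justify redrawing the constructs already named.

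5. *Detail left for later.* Which data the factor analysis uses could properly be set in a statistical analysis plan. The retention rule, rotation, cut-offs and purpose are fixed in the protocol and can be judged there.

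**Conclusion.** The point holds as a minor one. What is certain from the text is that 3.7.1 scores pre-set concepts, lets an exploratory procedure redefine them, describes that as confirmation, and does not say which prevails.

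The size of the harm is conditional. At n = 810 the eigenvalue rule can over-extract with loadings of about 0.4 to 0.6 and longer scales; it is right or nearly right from about 0.65 upward, and for short scales at 0.6. It would be too strong to say that the rule over-extracts here, because item counts and loadings are assumed. Where it does, the likely result is split, shortened or lost scales, not invented constructs.

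Research question 2 and the health motivation outcome are exposed. The latter is a secondary outcome in 3.6.3 but is absent from the outcome list in the Fig. 3 flow chart. Screening uptake is not scored from these scales and is unaffected. A reader might also infer damage to the path analysis in 3.9, but that section does not say that factor-derived constructs enter it.

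**What to change.** In 3.7.1:
- State that the pre-set HBM scoring key prevails, and test it by confirmatory factor analysis on the pretest data or on baseline data pooled over arms.
- Limit exploratory analysis to Phase 1 items that have no construct. For these, replace eigenvalue above one by parallel analysis, and varimax by an oblique rotation, which comes close to the orthogonal solution if the factors are in fact uncorrelated.
- Use the same item lists at baseline, three months and six months.

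The cost is a few sentences and a little more analysis work; no further data are needed. If the confirmatory model fits poorly, this should be reported with the results for research question 2, and any revised scale shown as a sensitivity analysis.

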**3.7.2. Procedures**

**3.7.2.1. Phase 1: Qualitative data for designing and development of community based intervention**

For this, first, focus group discussion with women and in-depth interview with health promotion and disease prevention experts, medical directors and health extension workers will be conducted by using a semi-structured checklists, which involves questions about currently challenging behavioral, cultural and social problems, facilitating factors and barrier of uptake of breast screening, ever used or currently predicted health promotion intervention applications and their characteristics, preferences of name and functional needs about a breast cancer screening message especially for women. Ideally, sample size of the qualitative will depend on the information saturation rule which means as sample expanding, no new theme be induced from information the participants supplied. A community based intervention will be prepared based on the results. Second, the research team will discuss on the issue and design the intervention considering feasibility, applicability and acceptability and expert experiences for the message delivering. Finally, community based intervention document will be determined and prepared. After the document is completed, we will invite the research team again to test it, necessary modification will be made accordingly.

